## Abstract

**Introduction:**

Recurrent urinary tract infections (RUTIs) have a significant negative impact on quality of life and healthcare costs. To date, daily prophylactic antibiotics are the only treatment which have been shown to help prevent RUTIs. D-mannose is a type of sugar which is believed to inhibit bacterial adherence to uroepithelial cells, and is already being used by some women in an attempt to prevent RUTIs. There is currently insufficient rigorous evidence on which to base decisions about its use. The D-mannose to prevent recurrent urinary tract infections (MERIT) study will evaluate whether D-mannose is clinically and cost-effective in reducing frequency of infection and symptom burden for women presenting to UK primary care with RUTI.

**Methods and analysis:**

MERIT will be a two-arm, individually randomised, double blind placebo controlled, pragmatic trial. Participants will be randomised to take D-mannose powder or placebo powder daily for 6 months. The primary outcome will be the number of medical attendances attributable to symptoms of RUTI. With 508 participants we will have 90% power to detect a 50% reduction in the chance of a further clinically suspected UTI, assuming 20% lost to follow-up. Secondary outcomes will include: number of days of moderately bad symptoms of UTI; time to next consultation; number of clinically suspected UTIs; number of microbiologically proven UTIs; number of antibiotic courses for UTI; quality of life and healthcare utilisation related to UTI. A within trial economic evaluation will be conducted to examine cost-effectiveness of D-mannose in comparison with placebo. A nested qualitative study will explore participants’ experiences and perceptions of recruitment to, and participation in a study requiring a daily treatment.

**Ethics and dissemination:**

Ethical approval has been obtained from South West-Central Bristol Research Ethics Committee. Publication of the MERIT study is anticipated to occur in 2021.

**Trial registration number:**

ISRCTN 13283516.

Strengths and limitations of this studyBased on current literature, this will be the first large publicly funded randomised controlled trial of D-mannose for prophylaxis of recurrent urinary tract infections.This study is the first to use a placebo control in evaluating the benefit of D-mannose.Obtaining the primary outcome by medical notes review will ensure data completeness.The trial may not be powered to detect a secondary outcome of symptom burden which is also of value to patient decision making.Although participants report weekly on their study product usage there are no objective measures available to confirm accuracy of reporting.

## Background

Urinary tract infection (UTI) is the most common bacterial infection that women consult for in UK primary care.^1 2^ Approximately 40%–50% of women experience one UTI episode during their lives.^3^ Recurrent UTIs (RUTIs) have a considerable negative impact on quality of life, which extends beyond the unpleasant symptoms to distressing and disrupted sexual relationships, persistent unmanageable pain and systemic illness.^4^ UTI accounts for an important proportion of healthcare costs as a result of outpatient visits, diagnostic tests and prescriptions.^5^ In 2007, UTI recurrence accounted for 10.5 million outpatient consultations and 2–3 million emergency department visits in the USA alone. In addition, UTIs are the most common cause of infection in hospitalised patients, accounting for 17.2% of all nosocomial infections in England. Furthermore, UTIs result in considerable patient morbidity and time off work; hence, the management of this condition incurs large financial costs, estimated at US$3.5 billion in the USA per year.^6^

A systematic review of randomised controlled trials identified antibiotic prophylaxis as the only treatment, which has been demonstrated to help prevent RUTIs. Antibiotics taken daily for 6–12 months were more effective than placebo at preventing recurrent infection,^7^ and national guidelines advocate their use for this indication.^8^ However, antibiotics also resulted in more severe and unpleasant side effects (eg, vomiting, urticaria, candidiasis). Furthermore, once antibiotic prophylaxis is discontinued, even after extended periods, approximately 50%–60% of women will experience a further UTI within 3 months.^9 10^ Thus, antibiotic prophylaxis does not exert benefit once stopped, and is directly linked to antibiotic resistance in uropathogens.^11^ Antibiotic resistance has been associated with an increased duration of severe symptoms of UTIs, irrespective of the use of an appropriate antibiotic.^2 11^

D-mannose is a type of sugar (a monosaccharide isomer of glucose), which is thought to inhibit bacterial adherence to uroepithelial cells by binding to a site on the tip of the fimbria^12^ and has shown benefit in animal models in preventing UTIs.^13^

Currently D-mannose is available commercially to the public as a food supplement, and is favoured by many women who have RUTIs, but until recently, there has been little empirical evidence to support its use. An open-label randomised three arm trial including 308 women with RUTI seen in outpatient settings^14^ found that daily use of D-mannose for 6 months resulted in an absolute reduction in incidence of further UTI of 45% from a proportion of 60% in the usual care arm, with no adverse events. The proportion of women experiencing an RUTI over 6 months was reduced by 11% compared with daily antibiotic use. This finding is supported by recent smaller studies.^15–18^

Although there are indicators of efficacy from small underpowered trials, the only adequately powered study to date^15^ was not placebo controlled and found an unexpectedly high RUTI incidence in the control arm. Furthermore, a microbiologically confirmed UTI was a requirement for entry to the study, and participants were withdrawn once they developed a UTI on treatment. Therefore, true incidence of UTI could not be established, a measure for women who experience frequent RUTIs, who are also the most likely candidates for prophylaxis. Finally, all women on hormonal contraception were excluded, which may reduce applicability to the women at high risk of RUTI.

D-mannose is found naturally in small quantities in numerous food sources, such as coffee, baker’s yeast, egg white, fruits such as apples, cranberries and mangos, and also in legumes such as soybeans, kidney beans and peanuts.^19^ It is absorbed in the upper gastrointestinal tract and excreted in the urine.^14^

D-mannose may offer an alternative to antibiotic prophylaxis in women who experience RUTI and in turn to contribute to better antimicrobial stewardship in primary care. However, the current evidence base is inadequate to help women with RUTI to make informed decisions about the use of D-mannose prophylaxis. The high costs (at least £25 a month) associated with its purchase add weight to the need to establish whether general practitioners (GPs) should advise their patients to use D-mannose for this indication.

The D-mannose to prevent recurrent urinary tract infections (MERIT) double blind placebo-controlled randomised controlled trial aims to evaluate the effectiveness of D-mannose in women suffering with RUTI presenting to UK primary care and its cost effectiveness.

## Methods and design

### Study aims, research questions and outcomes

The primary aim of MERIT is to assess the effectiveness of daily use of D-mannose compared with placebo in preventing symptomatic UTI in women.

The primary outcome of the trial will be the proportion of women experiencing at least one further episode of clinically suspected UTI for which they contact ambulatory care (out of hours primary care, in hours primary care, ambulance or the emergency department) within 6 months of study entry.

Secondary outcomes will include (within 6 months of study entry):

Number of days of moderately bad (or worse) symptoms of UTI.Time to next consultation with a clinically suspected UTI.Number of clinically suspected UTIs.Number of microbiologically proven UTIs.Number of antibiotic courses for UTI.Report of consumption of antibiotics using diary during periods of infection.Proportion of women with a resistant uropathogen culture during an episode of acute infection.Hospital admissions related to UTI.Quality of life and healthcare utilisation related to UTI.Healthcare utilisation recorded in the participant diary and during a notes review.Acceptability and process evaluation conducted via telephone interviews (after 6 months).

### Study design and setting

A two-arm, individually randomised, double blind placebo controlled, pragmatic trial. At least 50 GP practices in England and Wales will be invited to take part in the trial. Recruitment will run from March 2019 to January 2020.

### Eligibility

This trial will recruit female participants over 18 years with a primary care clinical record of having presented to ambulatory care with RUTIs three or more times in the last year or two or more times in the last 6 months. Exclusion criteria are: participants who are pregnant, lactating or planning pregnancy during the course of the study; formal diagnosis of interstitial cystitis or overactive bladder syndrome; prophylactic antibiotics started in the last 3 months and unwilling to discontinue, or intention to start in the next 6 months; currently using D-mannose and unwilling to discontinue for the duration of the study; nursing home resident; catheterised, including intermittent self-catheterisation; use of uromune; participation in a research study involving an investigational product in the past 12 weeks.

### Baseline assessment

Participants will have a baseline assessment (either in person with their GP or research nurse online, or by telephone with a member of the research team). During the baseline assessment the study will be explained, informed consent (see online supplemental file 1) will be obtained and data will be collected (see box 1). Participants will also be asked to send in a urine sample (when they are asymptomatic of a UTI) at baseline and have the option to also send in a perineal swab sample.

10.1136/bmjopen-2020-037128.supp1Supplementary data

Box 1Data collection throughout the trialBaseline:1. Demographic questions: including age.2. Medical history (by patients).3. Use of contraceptives and hormonal treatment.4. Urinary tract infection (UTI) episodes in the last 12 months.5. EuroQol 5-dimensional questionnaire (EQ-5D-5L).Weekly contact/monthly contact:1. UTI episodes in last week/month, respectively.Daily UTI diary1. UTI symptoms.2. UTI treatment.3. EQ-5D-5L.Six month questionnaire1. UTI episodes in the last month.2. EQ-5D-5L.Notes review and urine culture result1. Recorded UTIs during the study period.2. Healthcare contact for UTIs recorded.3. Antibiotics given for UTIs recorded.4. Culture results for UTIs recorded.5. Unscheduled hospital admissions.

### Randomisation

After the baseline assessment, participants will be randomised by a member of the research team using a validated internet based randomisation system with an emergency randomisation list available. Randomisation will use variable block sizes and will be stratified by GP practice ensuring a balance of the two arms within each practice.

### Intervention and placebo groups

Placebo will consist of two grams of a sugar powder which is similar in texture and taste to D-mannose but fully absorbed by the liver to be taken daily for 6 months.

Intervention will consist of two grams of D-mannose powder to be taken daily for 6 months.

An adequate supply of the study product will be sent directly from the research team to the participant after randomisation, after 2 months and after 4 months.

### Follow-up

All participants will be asked to complete short weekly questionnaires, sent to them via text or email; they also will have the option of completing them telephonically directly with the research team. The weekly questionnaire will collect the information of participant’s adherence to study medication, and whether the participant has had any symptomatic UTI episodes. Participants will also be contacted monthly by phone by the research team to complete a monthly questionnaire which is similar to the weekly one if there are two or more weekly questionnaires not being completed. They will also be asked to complete a daily UTI symptom diary if they experience a UTI. The information will be collected via weekly and monthly contact if they fail to complete the symptom diary although they experience one. During a UTI they will be asked to send the lab a urine sample, alongside any sample they might provide to their GP. They will also be asked for a further urine sample 2 days after symptoms have resolved. See box 1 for details. Primary care electronic medical record reviews will be conducted to collect UTI related healthcare contacts, culture results and prescriptions during the following up period. Participants will receive a £10 voucher after every 2 months of participation (£30 pounds in total). See figure 1 for the participant flow through the trial.

**Figure 1 F1:**
[figure not shown]
Flow through the trial. CRF, case report form; EOI, expression of interest; GP, general practitioner; RN, research nurse; UTI, urinary tract infection.

### Sample size considerations

A recent study to evaluate prophylactic treatment for RUTI in a similar population^20^ found that 26.6% of women in the control arm experienced an RUTI within 6 months. Our patient and public involvement advisors suggested that in order to commit to daily use of a prophylactic regime, they would require evidence of at least a 50% reduction in the chance of a further UTI during the period of prophylaxis. To detect this reduction with a two-sided Fisher’s exact test with 90% power and an alpha of 0.05 we would require 203 participants in each arm. This equates to 508 participants if a 20% loss to follow-up is assumed. This sample size is also adequate to power the key secondary outcome (the number of RUTI’s experienced over 6 months), and detect a relative incidence rate of 0.5 between the treatment and placebo groups, assuming a base rate of 0.36 as estimated by Maki *et al*.^20^ If the estimated percentage of participants who have either withdrawn or failed to respond to any study team communication for an extended period seems likely to rise above the 20% initially allowed for, we will recruit additional participants, up to a maximum of 598 participants.

### Statistical analysis

The primary outcome, the proportion of women experiencing at least one further episode of UTI symptoms for which they visited their GP within 6 months of study entry, and other binary outcomes, will be analysed on an intention-to-treat basis by means of a generalised linear mixed effects model with binomial distribution and log link function, including a random effect for practice and fixed effect for randomisation group. Therefore, treatment groups will be compared on the basis of an adjusted risk ratio. The number of days of moderately bad symptoms of UTI, the number of UTI’s experienced in 6 months, and number of antibiotic courses for UTI in 6 months, will be analysed by means of a generalised linear mixed effects model using the Poisson distribution and log link function, including a random effect for practice and a fixed effect for randomised group. Defined daily ooses (DDDs) will be analysed by means of a linear mixed-effects model including a random effect for practice and fixed effects for randomised group and baseline DDD, treating this outcome as continuous. We will analyse the overall DDD as well as the individual antibiotic DDDs.

The amount of missing primary outcome data is expected to be very low as it is collected via notes review. The model chosen to analyse the primary outcome implicitly accounts for data missing at random, however, the data missing mechanism will be explored. Summary statistics will be presented for baseline covariates of those participants who completed and those who were lost to follow-up for the primary outcome. Baseline covariates associated with missingness will be identified by analysing each baseline covariate in a logistic regression model to determine which (if any) are associated with missingness of the primary outcome. The associated p value will be reported alongside the summary statistics. Any baseline factors found to be associated with missingness of the primary outcome will be included in a sensitivity analysis.

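### The primary outcome is defined inconsistently: the outcomes section counts any ambulatory-care contact, the analysis section only GP visits, and the abstract names a count

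*Protocol article*

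**What the plan says.** The protocol article states the primary outcome in three places.

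- **Study aims, research questions and outcomes:** "the proportion of women experiencing at least one further episode of clinically suspected UTI for which they contact ambulatory care". The settings are then listed in brackets: "out of hours primary care, in hours primary care, ambulance or the emergency department) within 6 months of study entry".
- **Statistical analysis:** the proportion of women with "at least one further episode of UTI symptoms for which they visited their GP within 6 months of study entry". This is analysed by a "generalised linear mixed effects model with binomial distribution and log link function", giving an adjusted risk ratio.
- **Abstract, Methods and analysis:** "The primary outcome will be the number of medical attendances attributable to symptoms of RUTI". The next sentence of the abstract gives the power for halving the chance of a further clinically suspected UTI, which is a binary quantity.

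The Sample size considerations section is also binary. It cites a study that "found that 26.6% of women in the control arm experienced an RUTI within 6 months" and takes as its target "at least a 50% reduction in the chance of a further UTI during the period of prophylaxis". It treats the number of recurrent UTIs over 6 months as the key secondary outcome.

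**The concern.** The sentence in the Statistical analysis section tells the analyst what to code as an event. It is narrower than the outcomes section in setting (the woman's GP, against four kinds of ambulatory service) and in mode (a visit, against a contact). Some women would change from event to non-event depending on which sentence is followed, and the primary risk ratio could change with them.

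The data do not force the choice. The notes review collects UTI-related healthcare contacts in general, so both versions can be derived from the same records. If the wording is not settled before the allocation is known, the definition could be chosen after the result has been seen. The abstract adds a smaller discrepancy by naming a count where the rest of the article has a proportion.

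**Working it through.** **1. The definitions side by side**

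| | Outcomes section | Statistical analysis | Abstract |
|---|---|---|---|
| Type | Proportion, at least one | Proportion, at least one | Count |
| Setting | In-hours and out-of-hours primary care, ambulance, emergency department | Their GP | Any medical attendance |
| Mode | Contact | Visit | Attendance |
| Event | Clinically suspected UTI | UTI symptoms | Symptoms of recurrent UTI |

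The outcomes and analysis sections agree on type and on the 6-month window. They disagree on setting and mode. The difference in the event itself is thin, because the stated aim is to prevent symptomatic UTI.

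**2. Which type the design figures belong to**

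Inputs from Sample size considerations: control risk p1 = 0.266; a 50% reduction gives p2 = 0.133; two-sided alpha 0.05; power 90%; Fisher's exact test; 20% loss.

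- Uncorrected: n = [1.960 × √(2 × 0.1995 × 0.8005) + 1.282 × √(0.266 × 0.734 + 0.133 × 0.867)]² / 0.133² = 187.6, so 188 per arm.
- Continuity-corrected: n' = (n/4) × [1 + √(1 + 4/(n × 0.133))]² = 202.4, so 203 per arm, as stated.
- Exact enumeration of the two-sided Fisher test at 203 per arm: power 90.5%.
- Total: 2 × 203 / 0.8 = 507.5, so 508, as stated.

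The stated figures reproduce for a binary outcome. They do not settle which contacts count, because the 26.6% is described only as women who experienced a recurrent UTI.

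**3. The count**

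The article separately claims adequate power for the number of recurrent UTIs, with base rate 0.36 and rate ratio 0.5. Assume that 0.36 is per 6 months and that there is no overdispersion. Then SE(log rate ratio) = √(1/(203 × 0.36) + 1/(203 × 0.18)) = 0.203, and power = Φ(0.693/0.203 − 1.960), or about 93%. Variance inflation of 1.25 to 1.5 lowers this to about 86% to 80%. This is a count of UTIs, not of attendances.

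**4. Illustration of the narrower definition**

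The documents give no share of contacts outside GP visits, so the share below is assumed. The relative reduction is held at 50%.

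| Control events still counted | Risks compared | Exact Fisher power, 203 per arm | Total for 90% power with 20% loss |
|---|---|---|---|
| 100% | 26.6% v 13.3% | 90.5% | 508 |
| 90% | 23.9% v 12.0% | 86.2% | 578 |
| 80% | 21.3% v 10.6% | 80.7% | 665 |
| 70% | 18.6% v 9.3% | 73.8% | 778 |

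The stated recruitment ceiling is 598.

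**The case against.** The strongest reply is that the GP-visit phrase is loose shorthand. The outcomes section is the proper place for the definition and lists the settings explicitly. Eligibility is also framed by presentation to ambulatory care. The notes review is not limited to GP visits, and the abstract's attendances are not either. Nothing says that out-of-hours, ambulance, emergency or telephone contacts are to be excluded. A reader might infer a deliberate exclusion, and the documents do not support that. What remains is that the shorthand sits in the sentence governing the primary model and conflicts with the definition it should repeat. Condensing a protocol for a journal explains missing detail, but not a conflicting definition.

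A reader might also infer that the article leaves it open whether the primary outcome is a count or a proportion. It does not. The outcomes section, the sample size, the binomial model and the abstract's own power sentence are all binary, and only one abstract sentence is out of line. Nor can one say that the sample size has no bearing on a count, since the article claims power for a count of UTIs and a simple Poisson check is compatible with that claim.

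The power illustration has limits. The 26.6% is not tied to any type of contact. A share of episodes is not a share of women, because a woman with several episodes needs only one GP visit to count. Primary outcome data are expected to be nearly complete, so more than 203 per arm may contribute.

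**Conclusion.** The inconsistency is real and concerns the primary outcome, so it should be resolved before the data are analysed. The substantive part is the disagreement between the outcomes and analysis sections over which contacts count. The abstract's count is a wording error against an otherwise consistently binary design.

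The effect on the result cannot be sized from the documents. If 10% to 30% of control events fell outside GP visits and the reduction stayed at 50%, power at 203 per arm would be 86% to 74% instead of 90.5%. That range rests wholly on the assumed share and is not evidence that the trial is underpowered. The sample size arithmetic is correct as stated.

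**What to change.** In the Statistical analysis section, replace the GP-visit wording with the outcomes-section definition, word for word: the proportion with "at least one further episode of clinically suspected UTI for which they contact ambulatory care", with the same four settings and the same 6-month window. In the abstract, replace the count with that proportion. Leave the secondary outcomes as listed. The number of clinically suspected UTIs and healthcare utilisation are already among them. A number-of-attendances outcome is not, and none needs to be added.

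The cost is wording only, to be settled before database lock. No new data are needed, because the notes review already collects UTI-related healthcare contacts. The binomial model, 203 per arm and 508 in total are unchanged.

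### The Poisson mixed model for symptom days, UTI counts and antibiotic courses ignores variation between women, so standard errors for these secondary outcomes will be too small

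*Protocol article*

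**What the plan says.** The Statistical analysis section names one model for three secondary outcomes. The sentence opens "The number of days of moderately bad symptoms of UTI, the number of UTI" and goes on to antibiotic courses; all three "will be analysed by means of a generalised linear mixed effects model using the Poisson distribution and log link function". Practice is the model's only random term, and arm its only fixed term. No woman-level random effect, dispersion parameter, negative binomial alternative or robust variance is named.

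Sample size considerations calls the number of UTIs over six months the key secondary outcome. It says that the sample is large enough to "detect a relative incidence rate of 0.5 between the treatment and placebo groups, assuming a base rate of 0.36". For the primary outcome it cites the same source for the statement that "26.6% of women in the control arm experienced an RUTI within 6 months".

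The Randomisation section stratifies by practice. The strengths and limitations list says that symptom burden also matters to patients' decisions, and that the trial may lack power for it.

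**The concern.** A Poisson model fixes the variance at the mean. With a practice random effect, this still has to hold among women in the same practice and arm. Two features of these outcomes work against it.

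- **Women differ.** Some are much more prone to UTI than others, so counts vary more than Poisson allows.
- **Symptom days are not separate events.** A woman with one UTI contributes a run of days, and most women are expected to contribute none. The total is a sum of clusters, and Poisson treats each day as an independent event.

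The practice effect does not help. Allocation is balanced within practice, so the treatment contrast is made within practices, and variation between women in the same practice goes straight into the error of that contrast. If that error is understated, a chance difference in UTI frequency, antibiotic use or symptom burden can be reported as an effect of D-mannose.

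**Working it through.** **Inputs from the article (Sample size considerations):** 26.6% of control women with at least one UTI in six months; base rate 0.36; 203 women per arm. **Assumptions, not in the article:** 0.36 is the mean number of UTIs per woman over six months; between-woman variation is gamma-distributed (negative binomial counts); days of qualifying symptoms per episode.

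**The plan's own figure.** The primary sample size reproduces. Fisher's exact test for 26.6% against 13.3% with 203 per arm has 90.5% power, and 406/0.8 = 507.5, rounded up to 508. No power figure is given for the count outcome.

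**Step 1: do 0.36 and 26.6% fit a Poisson distribution?** A Poisson mean of 0.36 implies 1 − exp(−0.36) = 30.2% with at least one UTI, against 26.6%. Fewer women affected at the same mean suggests that UTIs are concentrated in fewer women.

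**Step 2: implied dispersion.** For a negative binomial with mean m and dispersion a, P(0) = (1 + m·a)^(−1/a). Setting m = 0.36 and P(0) = 1 − 0.266 = 0.734 gives a = 0.96. Variance/mean = 1 + m·a = 1 + 0.36 × 0.96 = 1.35.

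**Step 3: type I error for UTI counts.** If the true variance is φ times the one that the model uses, a nominal two-sided 5% test rejects with probability 2·[1 − Φ(1.96/√φ)]. With φ = 1.35, 1.96/√1.35 = 1.69, giving 9.1%. The result depends on the mean used:

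| Effective six-month mean | Variance/mean | Type I error |
|---|---|---|
| 0.36 | 1.35 | 9.1% |
| 0.34 | 1.21 | 7.4% |
| 0.32 | 1.07 | 5.8% |

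**Step 4: symptom days.** Let each episode contribute D days, and let v be the variance/mean of the episode count. For the total, variance/mean = E[D²]/E[D] + E[D]·(v − 1). With a fixed length d this is d + d(v − 1) = d·v. Poisson episodes (v = 1) therefore give a ratio equal to the episode length.

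| Days per episode (assumed) | Ratio, Poisson episodes | Type I error | Ratio, v = 1.35 | Type I error |
|---|---|---|---|---|
| 2 | 2.00 | 17% | 2.69 | 23% |
| 3 | 3.00 | 26% | 4.04 | 33% |
| 5 | 5.00 | 38% | 6.73 | 45% |

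Episode length that varies raises these further, since E[D²]/E[D] then exceeds E[D]. With mean 5 and SD 3, for instance, the two error rates become 45% and 50%.

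**Step 5: simulation of the stated model under no effect.** The Poisson mixed model with a random practice intercept was fitted to 406 women in 50 practices, or 90 where noted, with arms balanced within practice.

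- Truly Poisson counts: 4.6% rejections, so the model is sound when its assumption holds.
- Negative binomial counts at the Step 2 dispersion: 7.7–9.0% with 50 practices, 10.6% with 90.
- Symptom days with varying episode length and the Step 2 dispersion: 27% (mean 2 days), 38% (3), 45% (4) and 48% (5).
- Robust variance on the same data sets: 4–6% throughout, apart from 7% in one run of 400.

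The excess therefore comes from variation between women and within-episode clustering, and the practice effect does not absorb it.

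The article gives no figure from which to compute dispersion for antibiotic courses. They follow from UTIs, so the same argument applies in kind.

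**The case against.** **The reading of 0.36.** A reader might infer that the planning figures prove overdispersion. They do not. The article gives no unit or denominator for the base rate. If 0.36 is a rate per unit of follow-up time and 26.6% is a crude proportion, incomplete follow-up in the source could explain the gap. Pure Poisson needs a mean of −ln(0.734) = 0.309, and 0.309/0.36 = 0.86, so a loss of 14% of follow-up time would do it. This stands: the 9% is conditional, and UTI counts alone would make a modest point.

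**Episode length.** A reader might also quote 30–50% false positives for symptom days as a property of the plan. The article gives no number of qualifying days per episode, so any such figure rests on an assumption. This stands for the size but not the direction. With fixed-length Poisson episodes, which need no between-woman variation at all, two days already give 17%.

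**Power.** It is tempting to say that the power claim for the key secondary outcome is wrong. At 203 per arm and a rate ratio of 0.5, power is 92.8% under Poisson and about 87% under the dispersion in Step 2. But the article calls the sample adequate without giving a power level or a variance assumption for this outcome, and 87% does not contradict that.

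**Detail left to the analysis plan.** Dispersion checks, fallback models and a term for time observed commonly sit in a statistical analysis plan, which is not at hand. The absence of a time-observed term is therefore no error here. The model itself is different, because the article names the distribution and the random effect. If followed as written, it gives the understated errors above.

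**Secondary outcomes only.** All the affected outcomes are secondary, and the article already cautions about power for symptom burden. That lowers the severity. It does not remove the fault, because a caution about low power does not warn of false positives.

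**Conclusion.** The point holds for the secondary count outcomes and should be fixed. As written, the model understates the uncertainty for symptom days, UTI counts and antibiotic courses. The binary primary analysis is not touched.

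- **Symptom days:** the nominal 5% error becomes about 17–38% for fixed episodes of 2–5 days with Poisson episode counts, and about 23–45% with the suggested between-woman dispersion. Episode lengths are assumed.
- **UTI counts:** about 6–9% for effective six-month means of 0.32–0.36, assuming a negative binomial and that the base rate and the 26.6% describe the same women over the same period.
- **Antibiotic courses:** same direction, size not calculable from the article.

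**What to change.** Replace the plain Poisson variance with one that allows for overdispersion, and keep practice in the model. For example:

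- UTI counts and antibiotic courses: a negative binomial mixed model with a random effect for practice and a fixed effect for arm.
- Symptom days: a ratio of means with robust (sandwich) or bootstrap variance.

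A woman-level random effect or a scaled variance would also meet the point for the counts. What matters is that one method is named before unblinding. If the analysis plan already does so, the two documents need only be brought into line.

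The change is to the analysis wording and a few lines of code, with no new data. The price is wider intervals, by a factor of √φ: about 16% for UTI counts if φ = 1.35 (√1.35 = 1.16), and about 1.4 to 2.6 times for symptom days over the tabulated ratios (√2.00 = 1.41, √6.73 = 2.59). The extra width is uncertainty that the Poisson model leaves out.
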